##### Oral omega-3 fatty acid supplement

Targeting inflammatory pathways provides a window of opportunity for parallel interventions (e.g. exercise) to take effect. Nutritional supplements with anti-inflammatory effects, e.g. omega-3 fatty acids, are associated with reduced chronic inflammation in patients with kidney failure and could inhibit the inflammatory cytokine pathways associated with cachexia [38].

Omega-3 fatty acids are considered a safe and potentially therapeutic treatment for patients at high risk of inflammation such as those with kidney cachexia. Each patient will receive a 12-week supply of omega-3 fatty acid oral capsules using a daily dose (1000mg natural triglycerides, eicosapentaenoic acid (EPA) 180 mg, docosahexaenoic acid (DHA) 120 mg twice daily) which has a proven safety profile, tolerability, reduces inflammatory markers, and attenuates muscle protein breakdown in haemodialysis patients [39]. The capsules will be given to patients during the initial home visit at the commencement of the study.

##### Weekly contact

Patients in the intervention arm, will be contacted weekly (or more if preferred) by a telephone. A log will be completed regarding their adherence to the exercise, dietary advice, and nutritional supplementation. Weekly contact will be carried out by a trained member of the research team. This contact will provide behavioural support, monitor adherence, address barriers, and reinforce the BCTs integrated into the intervention.

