#### Control arm (standard care)

Patients in the control arm will not be offered the MMIEAD intervention and will receive standard care alone. The control arm will complete the assessments (see the ‘outcomes’ section below) at the three timepoints (baseline, 6, and 12 weeks). Patients who have been allocated to the control group will continue to receive routine standard care throughout the study. As the recruitment sites cover four hospital sites, a description of standard care per recruitment site will be collected as part of the process evaluation.

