### Data collection

To ensure consistency across the four study sites, all outcome assessors have undertaken standardised training before data collection begins, with refresher training provided as required. Harmonised data collection protocols, standard operating procedures, and uniform measurement tools will be used across all locations. Regular cross-site monitoring and fidelity checks will be conducted to ensure adherence to procedures and to minimise measurement error.

#### Phase 1

All eligible patients in both intervention arms and control arm will be required to complete baseline and follow up data at 6 weeks and 12 weeks. Longer-term survival (at 6 months and 12 months from the date of recruitment) will also be recorded. Adverse events (AEs) and serious adverse events (SAEs) will be reported using a standard procedure and relatedness will be determined by the clinical team as per our ethically approved reporting structure.

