**Effectiveness**			
Overall feasibility	Adherence data – exercise diaries, 3-day food diaries, tablet count (intervention sites only) Weekly log (from phone calls) Outcome measures Record of AEs and SAEs Patient interviews	% of patients who completed exercise diaries and 3-day food diaries. Nutritics for diet analysis, assess adherence to dietetic advice % of patients who consumed recommended intake of omega-3 fatty fish oil. Identify reasons why adherence potentially affected % outcome measures completed % of related AEs/SAEs Burden of outcome measures	Intervention characteristics: Was MMIEAD adaptable to each individual patient and does it indicate that it is beneficial without causing any harm? (intervention only) Recipient experience: Did patients’ perceptions indicate that the MMIEAD intervention could improve QoL? (intervention only)
Variations in feasibility	HCP interviews	Identify barriers, facilitators, potential reasons for variations in feasibility.	
Patients’ satisfaction with the intervention (intervention sites only)	Patient interviews	Questions on acceptability of trial organisation, physical activity dietary advice, nutritional supplement weekly support.	

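### Weekly research calls in the intervention arm only may raise the recorded frequency of non-serious, patient-reported adverse events there with no true difference; serious events should be little affected

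*Protocol article*

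**What the plan says.** Under Weekly contact, the protocol article states: "Patients in the intervention arm, will be contacted weekly (or more if preferred) by a telephone". On content it says "A log will be completed regarding their adherence to the exercise, dietary advice, and nutritional supplementation", and on purpose "This contact will provide behavioural support, monitor adherence, address barriers, and reinforce the BCTs integrated into the intervention". Adverse events are not mentioned there.

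Under Control arm (standard care): "The control arm will complete the assessments (see the ‘outcomes’ section below) at the three timepoints (baseline, 6, and 12 weeks" and "Patients who have been allocated to the control group will continue to receive routine standard care throughout the study". No matching weekly contact is described for controls.

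Under Data collection, Phase 1, which covers both arms: "Adverse events (AEs) and serious adverse events (SAEs) will be reported using a standard procedure". The clinical team judges relatedness.

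In Table 3, the overall-feasibility row of the Effectiveness dimension lists the weekly telephone log and the record of adverse events among its sources. Its measures include "Identify reasons why adherence potentially affected" and the percentage of related events. Multi-method integration then has each RE-AIM outcome rated as positive, negative or mixed, and the ratings compared between intervention and control.

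**The concern.** An event has to be heard before it can be recorded or judged related. A weekly conversation about why exercise, diet or capsules were missed is a natural occasion for a patient to mention a fall, nausea or a bad week. Controls have no study regimen to miss, so no parallel conversation arises. The trial is unblinded (Blinding section), and Strengths and limitations itself expects deteriorating health to affect adherence.

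A single reporting procedure governs what is done with an event once it is known. It does not by itself equalise the chances of its becoming known. Restricting the count to related events does not remove the problem either, because detection comes before the judgement of relatedness.

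Two misreadings are possible. An excess of minor events under MMIEAD could be taken as a safety signal when it reflects extra contact, or a real excess could be put down to extra contact. In either case the definitive trial would lack a comparable rate of non-serious events by arm.

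**Working it through.** The article states no adverse event rate, so there is no planned figure to reproduce. The check has three steps.

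**1. Scheduled research contacts after baseline, over 12 weeks**

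- Intervention: 12 weekly calls + 2 assessments = 14. If the calls in weeks 6 and 12 are merged with the assessments, 12. The physiotherapist and dietician reviews at 6 weeks are not counted.
- Control: 2 assessments.
- Longest gap between research contacts: 1 week against 6 weeks.
- Routine dialysis contact is common to both arms. It is left out of these counts and enters step 3.

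**2. Is there a between-arm reading for this to distort?**

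Table 3 places the event record under Effectiveness, and Multi-method integration compares the RE-AIM ratings across intervention and control to inform the definitive trial. A descriptive comparison is therefore planned. No statistical test of adverse events is stated.

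**3. Illustration of size, with equal true rates**

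Assumptions, none of them from the documents:

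- A share h of events becomes known through routine dialysis care in either arm.
- Each remaining event is reported at the next research contact with probability exp(−t/τ), where t is the number of weeks since the event.
- A call records an event as readily as a visit does.

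Mean capture over a gap of L weeks is C(L) = h + (1 − h) × (τ/L) × (1 − exp(−L/τ)). The apparent ratio is C(1)/C(6).

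Example with h = 0.5 and τ = 4:

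- C(1) = 0.5 + 0.5 × 4 × (1 − exp(−0.25)) = 0.94
- C(6) = 0.5 + 0.5 × (4/6) × (1 − exp(−1.5)) = 0.76
- Ratio = 1.24

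| Share known through routine care (h) | τ = 2 weeks | τ = 4 | τ = 8 | τ = 26 |
|---|---|---|---|---|
| 0 | 2.48 | 1.71 | 1.34 | 1.10 |
| 0.5 | 1.36 | 1.24 | 1.14 | 1.05 |
| 0.8 | 1.11 | 1.08 | 1.05 | 1.02 |
| 1 | 1.00 | 1.00 | 1.00 | 1.00 |

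Under this model the ratio is never below 1. The bottom row describes events that the dialysis unit would know of anyway, such as deaths and admissions. If the calls give rise to no event records at all, the ratio is 1.00 throughout.

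**The case against.** Several stronger readings are tempting, and the article does not support them.

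- **A reader might infer that controls are seen only at weeks 6 and 12.** Those are the research assessments. Controls are maintenance haemodialysis patients who keep attending their units, with monthly bloods. This stands and narrows the gap. It does not close it, because intervention patients attend dialysis as well and have the calls in addition.
- **A reader might infer that controls are never asked about adverse events.** The article refers to a standard procedure within an ethically approved structure but does not reproduce it. A condensed article may leave such detail to the full protocol, and its silence shows nothing about what controls are asked. This stands. The point rests only on the contact schedules that the article does state.
- **The weekly call is described as an adherence log, not as a safety enquiry.** This is correct. That it will bring out symptoms is likely but not stated. In Table 3, the reasons for affected adherence sit in a row with several sources, not with the calls alone.
- **A reader might infer that an all-cause count by arm is planned and will be inflated.** The only measure named is the percentage of related events, the question about harm in Table 3 is marked as applying to the intervention only, and no significance claims are intended. This limits the reach of the point. What remains is the comparison of Effectiveness across arms, which draws on the same record.
- **A common question at shared visits would not fully equalise recall.** This stands: patients who have already discussed an event on a call, or noted it in an exercise diary, may remember it better.

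**Conclusion.** The point holds in a limited form. Scheduled research contact is unequal by design, about 14 against 2, and this may raise the recorded frequency of non-serious, patient-reported events in the intervention arm when there is no true difference. The direction is upward or neutral.

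The size depends on inputs that the documents do not give. It runs from 1.0 to about 2.5 over the assumptions tried, and from 1.05 to 1.36 if half of events come to light through routine care. Where routine care catches 80%, the ratio is at most 1.11, so a negligible effect is among the plausible results.

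It would go too far to say that the trial can give no usable event rates by arm. Survival is taken from medical notes, and serious events and admissions should be known to the dialysis units in both arms. What is at risk is a comparable rate for minor events, in 20 patients per arm.

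**What to change.** Base any between-arm summary of adverse events on events ascertained in the same way in both arms:

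1. At the existing week 6 and week 12 assessments, put the same scripted question with the same look-back to every patient. If the full protocol already provides this, say so.
2. Take serious events, admissions and deaths from the medical notes in both arms, from baseline to week 12.
3. Add a source field to the event record (assessment, notes or weekly call).
4. List events first heard on weekly calls separately, outside the between-arm count. They are still recorded and handled for patient safety.

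The cost is one form item at two visits that already take place, one extra field and a notes check. No visit is added. Recruitment has begun, but notes can be reviewed retrospectively, and events already recorded may be traceable to calls through the weekly log. The downside is that mild events heard only on calls leave the between-arm count, though they remain listed. Some difference in recall between arms may persist and should be acknowledged when the results are reported.

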#### Control arm (standard care)

Patients in the control arm will not be offered the MMIEAD intervention and will receive standard care alone. The control arm will complete the assessments (see the ‘outcomes’ section below) at the three timepoints (baseline, 6, and 12 weeks). Patients who have been allocated to the control group will continue to receive routine standard care throughout the study. As the recruitment sites cover four hospital sites, a description of standard care per recruitment site will be collected as part of the process evaluation.

#### Processes

##### Recruitment (phase 1 and 3)

Our recruitment rate is anticipated to be two patients per month per site. The sample size for the feasibility study is 40 patients, collectively 20 per intervention arm, 20 per control arm, based on providing sufficient information to inform the primary outcomes [40]. The study is being supported by Northern Ireland Clinical Research Network (NICRN).

##### Recruitment for the process evaluation (phase 2)

Approximately 15 patients will be recruited into the process evaluation. Approximately five patients from control, five intervention completers (across both intervention sites), and five intervention non-completers (across both intervention sites).

Approximately 15 healthcare staff across all sites will be recruited into either focus groups or individual interviews, with a proposed total of three focus groups. The focus groups will be limited by the number of staff available who meet the eligibility criteria and the requirement to produce a manageable amount of data for the time limitations of the study.

Data saturation will be reached when no new themes are found within the data [41] (see Fig. 1).

**Fig. 1 Fig1:**
[figure not shown]
Study flow diagram

### Data collection

To ensure consistency across the four study sites, all outcome assessors have undertaken standardised training before data collection begins, with refresher training provided as required. Harmonised data collection protocols, standard operating procedures, and uniform measurement tools will be used across all locations. Regular cross-site monitoring and fidelity checks will be conducted to ensure adherence to procedures and to minimise measurement error.

#### Phase 1

All eligible patients in both intervention arms and control arm will be required to complete baseline and follow up data at 6 weeks and 12 weeks. Longer-term survival (at 6 months and 12 months from the date of recruitment) will also be recorded. Adverse events (AEs) and serious adverse events (SAEs) will be reported using a standard procedure and relatedness will be determined by the clinical team as per our ethically approved reporting structure.

##### Primary outcome

Recruitment is measured as the number of fully enrolled patients as a proportion of approached eligible individuals. The appropriateness of this outcome in a feasibility study is highlighted in the literature [42]. Retention will be assessed by the proportion of patients screened vs. those consented and attrition rates (at 6 weeks and 12 weeks).

In order to test data collection techniques and suitability of outcome measures, secondary outcomes include demographic data (including age, height to calculate BMI), dialysis vintage, and co-morbidities (Charlson comorbidity index (CII)) [43]; these will be collected at baseline only. The following outcomes will be collected from all patients prior to commencement (baseline), midway (6 weeks), and on completion (12 weeks) of the intervention:

##### Physical function

The Short Physical Performance Battery (SPPB) [44] will provide co-efficacy endpoints of both muscle strength and functionality which are clinically meaningful outcome measures for sarcopenia and frailty and well established in haemodialysis patient populations. More specifically, the Edmonton Frail Scale (EFS) [45] will be included which is validated for use in haemodialysis population.

##### Body weight/weight loss

Unintentional weight loss by body weight (kg) monitoring will be recorded [46].

##### Muscle mass

Three methods of muscle mass will be used including bioelectrical impedance analysis (BIA) using a calibrated dual-frequency (5 and 50 kHz) Bodystat 1500 MDD device (Bodystat, Isle of Man, UK). A standard protocol will be followed with BIA assessment post-dialysis to control for variation in fluid status [47]. Measurements will be taken in the supine position, with electrodes attached on the hand and foot contralateral to the side of the arteriovenous fistula, and at constant room temperature. Patients with any implantable electronic devices (such as pacemakers) will be excluded from this assessment as per the manufacturer’s guidelines. For those patients who complete the BIA, a measure of BMI will be calculated using the clinical formula weight (kg)/height (m^2^). Mid-arm circumference (MAC) and triceps skinfold (TSF) thickness (TSF in triplicate and the average calculated) will be measured in the non-fistula arm using a tape measure and Harpenden skinfold calliper set respectively. The mid upper arm muscle circumference (MUAMC) will be calculated using the formula MAMC (cm) = MAC (cm) - 0.314 × TSF (mm). Suitable cut-point values designated the 5th percentile as an appropriate cut-point for low MUAMC using normative values (i.e. <23.8 cm for males and <18.4 cm for females) [48, 49] which will provide reliable and valid assessment of muscle mass in the absence of gold standard techniques (e.g. DEXA, MRI or CT). Combining these assessments reduces measurement error and normative values are well established in haemodialysis patient populations [50].

##### Muscle strength

Handgrip strength (HGS) will be measured using a KERN MAP 80K1S hand grip dynamometer which is an ideal device to determine reduced hand strength. A hand grip dynamometer is a highly reliable measurement tool in patient populations and established as a valid tool in haemodialysis populations [47]. We will be using a standard protocol (dominant arm, seated position with elbow at 90°, allowing three attempts) [51]. Specific cut-off points will be applied based on the European Working Group for Sarcopenia in Older People (EWGSOP) for muscle strength (<27 kg for males and <16 kg for females) [52].

##### Fatigue

The Functional Assessment of Chronic Illness Therapy (FACIT-F) [53] has been used extensively in kidney disease. Brown et al. [54] reported strong correlations between the “chair-rise” time test and FACIT, suggesting that it is a reliable measure of physical function. Lower scores of the FACIT subscale refer to lower function and thus increased fatigue. The optimal cut-off value for FACIT is <30 [55].

##### Appetite

Appetite will be recorded using the Functional Assessment of Anorexia/Cachexia Therapy (FAACT) tool [56]. The optimal cut-off value for the FAACT is <32 [57]; lower scores on FAACT reflect poor appetite. This tool has been used extensively in patient populations and is regarded as a reliable and valid tool in haemodialysis patients and suitable for measuring appetite in patients with cachexia [47].

##### Routine blood values and biomarkers

These include blood values and biomarkers from routine collected bloods including the following: C-reactive protein (CRP), serum albumin, urea reduction ratio (URR), estimated glomerular filtration rate (eGFR), and haemoglobin.

##### Quality of life

Health-related quality of life (HRQOL) has become increasingly important as an outcome measure of kidney replacement therapy, peritoneal dialysis, and transplant. HRQOL among haemodialysis patients has been shown to be lower as compared to pre-dialysis populations, the general population, and other chronic disease populations such as congestive heart failure, diabetes, depression, and even cancer. HRQOL is also poorer in cachectic patient populations and therefore an important criterion [10]. The 36-item Kidney Disease Quality of Life scale (KDQoL-36) will also be administered to patients in conjunction with EQ-5D-5L at baseline, post-intervention, and at 6 weeks and 3 months follow-up (this will be used in conjunction with Modular resource Use Measure (MODRUM), see phase 3). The EQ-5D-5L is recommended by the National Institute of Clinical Excellence (NICE) for deriving utility values for the calculation of quality adjusted life years in cost-effectiveness analysis within definitive economic evaluations [58] and has been shown to be a valid measurement of health status in patients receiving haemodialysis [59].

##### Mortality

Survival will be recorded 6 and 12 months from the date of recruitment, and data will be generated from patients’ medical notes.

#### Phase 2

The process evaluation will follow the MRC guidance on process evaluations for complex evaluations [60] informed by the PRISM/RE-AIM framework [26]. It will therefore focus on the acceptability of the intervention, barriers and facilitators to implementation, the appropriateness of outcome measures, motivations for participation, reasons for continued engagement, and potential mechanism of impact of the intervention. The interviews will be conducted in person, and the guides will be flexible to ensure that participants can express and explore perspectives that they consider relevant to implementation. The interviews will be used to examine the fidelity and quality of implementation, and how the intervention effects are mediated by different settings and contexts. It will also examine acceptability and unintended consequences.

#### Phase 3

Healthcare resource use of patients will be collected using MODRUM [61]. This measure will collect information on health and social care service use pre and after the intervention. The measure will be used at baseline and 3 months follow-up. The outcome of interest will be the feasibility of using a healthcare resource use log in a full economic evaluation according to proportion of patients who complete the healthcare resource use log. The evaluation of costs related to the intervention and implementation, in addition to any operational costs, will provide important information on adoption and implementation in RE-AIM [27].

### Ethics and rigour

This study has been approved by National Health Service (NHS)/Health and Social Care (HSC) Research Ethics Committee (REC reference: 25/NI/0069). To ensure informed consent is obtained freely from participants (both patients and HCPs), they will initially be approached by the local collaborator on site, who will provide them with a verbal summary of the project and the participant information sheet (PIS). Essential aspects of good practice, including clear and sensitively written participant facing materials’ voluntary participation, and informed consent will be employed as a minimum standard. All data will be stored for a minimum of 5 years and subsequently destroyed in accordance with the data protection act [62]. The trial will be conducted in accordance with the protocol as registered on clinical trials (NCT07107087) the principles of the Declaration of Helsinki and Good Clinical Practice (GCP). Medicines and Healthcare Products Regulatory Agency (MHRA) have agreed that the supplement (omega-3 fatty acids) is not a Clinical Trial of an Investigational Medicinal Product (IMP) as defined by the EU Directive 2001/20/EC. The end of the study will be defined as the date of the last visit of the last participant or the completion of any follow-up monitoring and data collection as described in the “Data collection” section.

